### Randomisation and blinding

Randomisation will be carried out using random permuted blocks. Computer-generated random numbers will be produced to select a block of allocations from the set of all possible permutations of allocations (on a 1:1 ratio) given a particular block size before the trial begins. Saint Mary’s Pharmaceutical Unit will undertake an exercise to validate the blinding process. A reproducible method that ensures all the fibrinogen does dissolve will be developed and detailed guidance produced that will form the basis of training the centre staff.

The fibrinogen concentrate will be supplied as vials of 1 g per bottle by CSL Behring to Saint Mary’s Pharmaceutical Unit (SMPU) in Cardiff. The placebo will be 50 ml of normal saline for each 1 g of fibrinogen. SMPU will supply each site with packs of blinded fibrinogen concentrate and placebo. At the time of randomisation the next consecutive numbered study pack will be opened. Black syringes will be used to draw the fibrinogen/placebo bottles with added diluents; the air will be expelled from the syringe into a bag of Gelofusine. SMPU has undertaken an exercise to validate the blinding process and ensure that all the fibrinogen dissolves.

### Observational phase

When women fulfil the study entry criteria they will enter the observational phase (Figure 2). Standard obstetric procedures for managing PPH (except those relating to blood product usage) such as suturing, removal of retained products and surgical or tamponade treatments for resistant atony will be followed according to local and national guidelines and are at the discretion of the treating clinicians. All other management will follow standard local procedures and is at the discretion of the treating clinicians. When women fulfil the criteria:

**Figure 2 Fig2:**
[figure not shown]
Observational phase.

Blood will be taken for full blood count (FBC), coagulation screen and group and save/cross match and sent to the routine laboratory for analysis. These tests are part of standard care.At the same time as the routine blood tests, an extra 5-ml sample will be taken into a coagulation screen bottle and a Fibtem test will be performed on a ROTEM machine located in the delivery suite or obstetric theatre.A measurement will be made of the blood loss according to the procedures described below as soon as possible after study entry.

If the Fibtem A5 is less than 16 mm, the bleeding is on-going and the baby has been delivered, the woman will enter the interventional phase. If the Fibtem A5 is 16 mm or above further Fibtem assays may be performed after each 500 ml additional blood loss or for clinical concern. If any subsequent Fibtem falls below 16 mm the woman will enter the interventional phase (Figure 3).

**Figure 3 Fig3:**
[figure not shown]
Interventional phase.

### Interventional phase

The participants are assigned either to placebo (isotonic saline) or interventional drug (fibrinogen concentrate, Riastap® CSL Behring, Marburg, Germany). The dose of fibrinogen concentrate or placebo to be infused will be calculated based on the woman's ideal body weight for height and the measured FIBTEM A5 with the aim of increasing the Fibtem A5 to 23 mm. The dose will be calculated as: dose (g) = (23-actual Fibtem A5) × ideal body weight for height/140. The dose will be rounded to the nearest whole number of grams of fibrinogen and the maximum dose of fibrinogen concentrate or placebo will be 8 g. At the time of randomisation the following will be done:Four units of FFP will be ordered from the blood bank through routine procedures.A measurement of blood loss will be made at the time the FFP is requested.Tranexamic acid (1 g) will be given intravenously, if not already given. A further dose of 1 g can be given intravenously if bleeding continues after 1 h of the initial dose. Women should then receive tranexamic acid 8 hourly, either orally or intravenously, for a period of time determined according to local practice.At about 15 min after the infusion of fibrinogen/placebo a coagulation screen and sample for a Fibtem will be sent to the routine laboratory. These results cannot be accessed by study staff until after the decision has been taken to give or withhold the FFP because they are likely to unblind the study. A clinician can decide to access these results if the clinical situation requires it but if this happens the woman would not be included in the primary efficacy analysis.Blood loss will be measured every 15 min, if feasible, until the FFP arrives.An additional Fibtem and coagulation screen will be taken at 24 h after the study medication, if possible coinciding with a routine FBC.

The decision to give FFP will be taken by a team approach after consultation with either a consultant obstetrician and or a consultant obstetric anaesthetist. The FFP will not be given if the bleeding has stopped and/or the bleeding is slowing and the total blood loss is less than 500 ml.

The FFP will be given if the bleeding is on-going and there has been a further measured 500 ml blood loss since the infusion of fibrinogen/placebo, if the bleeding is on-going and the amount of bleeding has not reduced between the first and last 15-min observation period following randomisation, and if the bleeding is on-going and microvascular oozing or cardiovascular instability is clinically apparent.

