### Outcomes and safety measures

The primary outcome is the total number of allogeneic blood products transfused after the study medication until discharge. The total number of allogeneic blood products transfused will be compared between the two arms. Secondary outcomes will be:the proportion of women receiving no allogeneic blood products until discharge and within 24 h after study medication,the number of units of red blood cells, FFP, platelets and cryoprecipitate transfused after study medication within 24 h and until discharge,the volume of cell salvaged blood transfused within 24 h after study medication and until discharge, the total number of units of red blood cells, FFP, platelets and cryoprecipitate transfused within 24 h after the study medication, the total number of units of red blood cells, FFP, platelets and cryoprecipitate plus 1 unit for every 250 ml cell salvage transfused within 24 h after study medication and until discharge, the measured abnormal blood loss within 24 h after study medication and until discharge, the proportion of women requiring cryoprecipitate or fibrinogen concentrate as subsequent therapy within 24 h after study medication and until discharge, the change in Clauss fibrinogen and Fibtem parameters before and 15 min and 24 h after the study medication, the proportion of women requiring invasive procedures (return to theatre, uterine brace sutures, uterine tamponade balloons, radiology intervention and hysterectomy) and the time of this intervention within 24 h after study medication and until discharge, incidence, duration and reasons for not exclusive breastfeeding.

The effects of fibrinogen concentrate infusion on the following safety endpoints will be explored: the proportion of women requiring high dependency and intensive care admission and length of stay, the total length of hospital stay and the incidence of clinically diagnosed arterial and venous thromboembolism within 6 weeks of study medication.

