### Interventional phase

The primary and secondary comparative analyses and presentation of this randomised trial will be in accordance with CONSORT guidelines and based on the intention-to-treat (ITT) principle without imputation of missing values (complete case population). The intention-to-treat population uses all randomised participants in the groups they were randomised to regardless of the intervention received and the complete case population restricts the population to include all randomised participants with complete data and follow-up. ITT analysis with missing values imputed will be undertaken as a sensitivity analysis.

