### Primary analysis

For those who enter the interventional phase of the study, the primary outcome will compare the total number of units of allogeneic products (red blood cells, FFP, cryoprecipitate, and platelets) transfused after study medication until discharge from hospital between women who received fibrinogen concentrate and placebo. A Poisson regression model will be used with due emphasis placed on confidence intervals for the between-arm comparisons with an investigation of site-level clustering. The primary analyses will also be repeated controlling for any baseline imbalances. While the main analyses will be based on ITT without imputation, we will undertake sensitivity analyses in order to estimate the effect of those randomised to fibrinogen but not receiving it using complier average causal effect (CACE) estimates, implemented in Stata using instrumental variable regression [24].

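### The rule that removes women from the primary efficacy analysis after early access to the 15-minute result contradicts the stated intention-to-treat analysis

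*Protocol article*

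**What the plan says.** Protocol article, Interventional phase (treatment and sampling). A coagulation screen and Fibtem sample are taken about 15 minutes after the infusion. The results are withheld: "These results cannot be accessed by study staff until after the decision has been taken to give or withhold the FFP", the reason given being "because they are likely to unblind the study". There is an exception, "A clinician can decide to access these results if the clinical situation requires it", with the consequence that "if this happens the woman would not be included in the primary efficacy analysis".

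Protocol article, Interventional phase (under the statistical methods). Primary and secondary comparisons follow the intention-to-treat principle without imputation. The starting population is defined first: "The intention-to-treat population uses all randomised participants in the groups they were randomised to regardless of the intervention received". One further limit is then set, for missing data only: "the complete case population restricts the population to include all randomised participants with complete data and follow-up". The Primary analysis section repeats that "the main analyses will be based on ITT without imputation".

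Protocol article, Outcomes and safety measures. "The primary outcome is the total number of allogeneic blood products transfused after the study medication until discharge".

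The Discussion accepts partial unblinding of women still bleeding after the first FFP, on safety grounds, and attaches no exclusion to it.

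**The concern.** Under the statistical section, a randomised woman leaves the primary analysis only if her data or follow-up are incomplete. Opening a laboratory result early does neither, because her units can still be counted to discharge. The statistical section therefore keeps her in and the sampling section takes her out. The exclusion names only the primary efficacy analysis, so the 24-hour total, a secondary outcome, would include her while the total to discharge would not.

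Two things are at stake. First, with two incompatible populations on record, the choice could be made after the results are known, in a trial of 60 women. Second, the exclusion acts after randomisation and after study drug. Its trigger is clinical need in a woman who was bleeding when randomised, and the outcome is units transfused. If access tends to follow worsening bleeding and the drug reduces bleeding, the rule removes more placebo than fibrinogen women and shrinks the estimated benefit.

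**Working it through.** **1. The plan's own sample size.** Inputs from the Sample size section, on the ln(x + 1) scale: means 1.811 and 1.036, difference 0.775, SD 1.004, two-sided 5%, power 80%.

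n per arm = 2 × [(1.960 + 0.842) × 1.004 / 0.775]² = 26.3, rounded up to 27. This agrees with the plan. Power at 27 per arm is 0.81 (0.795 with the noncentral t). 54 / 0.9 = 60, as stated. No stated figure is wrong. The 10% allowance is described as loss to follow-up and does not mention these exclusions.

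**2. Exclusion unrelated to outcome.** Losing 1, 3 or 5 women per arm beyond the allowance leaves 26, 24 or 22, with power 0.795, 0.762 and 0.726. The expected difference stays at 0.775.

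**3. Exclusion related to outcome.** The documents give neither an access rate nor its link to outcome, so both are assumptions. Take normal outcomes on the design scale and a latent severity with correlation ρ to the outcome. A result is opened when severity passes one threshold, the same in both arms.

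- Placebo threshold: c = z(1 − p), where p is the placebo access rate. Fibrinogen threshold: c + ρ × 0.775 / 1.004.
- With h = φ(c) / Φ(c), the mean of the women who remain is μ − 1.004 × ρ × h.
- Their SD is 1.004 × √[1 − ρ²(c × h + h²)].
- Power = Φ(difference / SE − 1.96), with 27 × (1 − access) women in each arm.

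Example with p = 10% and ρ = 0.7:

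- Placebo: c = 1.282, h = 0.195, mean 1.811 − 0.137 = 1.674, SD 0.930, 24.3 women.
- Fibrinogen: c = 1.822, h = 0.079, mean 1.036 − 0.056 = 0.980, SD 0.967, 26.1 women (3.4% removed).
- Difference about 0.69. SE = √(0.930² / 24.3 + 0.967² / 26.1) = 0.267. Power 0.74.

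| Placebo access | ρ | Fibrinogen access | Difference | Power |
|---|---|---|---|---|
| 5% | 0.4 | 2.5% | 0.76 | 0.78 |
| 5% | 0.9 | 1.0% | 0.70 | 0.76 |
| 10% | 0.4 | 5.6% | 0.74 | 0.76 |
| 10% | 0.7 | 3.4% | 0.69 | 0.74 |
| 10% | 0.9 | 2.4% | 0.65 | 0.71 |
| 20% | 0.4 | 12.5% | 0.73 | 0.71 |
| 20% | 0.9 | 6.2% | 0.58 | 0.63 |

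**4. No drug effect.** The outcome distribution and the threshold are then the same in both arms, so the expected difference among the women who remain is zero and only numbers are lost.

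**The case against.** **The exclusion has a reason.** Knowing the result is likely to influence whether FFP is given, and FFP counts in the primary outcome. The Discussion makes this point. It stands as a reason to record early access and examine its effect. It does not justify removing randomised women from the primary comparison, and the article accepts later partial unblinding without removing anyone.

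**The window is narrow.** The rule is best read as covering access before the first FFP decision only. FFP is ordered at randomisation and usually takes around 60 minutes to arrive. Laboratory fibrinogen takes 60 to 90 minutes, so that result may often come after the decision. FFP can also be given on clinical grounds without the result. This stands, and it argues against assuming a high access rate. The window is not empty, because a Fibtem A5 can be available within 10 to 15 minutes of sampling.

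**The severity link is inferred.** A reader might conclude that the rule removes the women with uncontrolled bleeding and the largest transfusion counts. The article names only clinical need as the trigger. The link is plausible but is not stated.

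**Losses in units can mislead.** A reader might take the Cardiff mean of 8.2 units (SD 8.7), drop three of 30 placebo women with heavy bleeding, find a mean of 7.2 or 6.1, and set that loss of 1.0 to 2.1 units against the design figure of 3.3. The scales differ: 3.3 is 5.12 − 1.81, a difference of back-transformed log means. Applying the planned shift to x + 1 gives 9.2 × exp(−0.775) − 1 = 3.2, an arithmetic difference of about 5.0 units. That illustration also drops nobody from the fibrinogen arm. The log-scale calculation avoids both problems.

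**Bias in either direction.** A reader might also infer that an ineffective drug could be made to look effective. With no drug effect and blinding intact, access cannot depend on arm. Bias of open direction would need cues that reveal the allocation before the result is opened.

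**Conclusion.** The contradiction is certain from the text: one section removes a woman whom the other keeps, and nothing in the article reconciles them. This is not detail left to an unseen analysis plan, because the protocol article itself fixes both rules.

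The size is conditional. At 10% placebo access and ρ = 0.7, the difference falls from 0.775 to about 0.69 and power from 0.81 to 0.74. Across 5% to 20% and ρ from 0.4 to 0.9, the ranges are about 0.76 to 0.58 and 0.78 to 0.63. The effect is modest at low access rates and material at the upper end. These figures assume a working drug, one access threshold for both arms, and the sample-size scale rather than the planned Poisson model. They take the exclusions out of the 27 per arm. If actual loss to follow-up were below 10%, the power loss would be smaller, but the shrinkage of the difference would remain.

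The expected direction, if access follows severity and the drug works, is towards the null. The documents do not support a claim that the rule produces false positives, or that it certainly removes the worst bleeders.

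**What to change.** Delete the exclusion from the primary analysis and state that every randomised woman with outcome data is analysed in her allocated arm, as the statistical section already says. Record each access before the first FFP decision as a protocol deviation, with time and reason, and report the counts by arm. Present the analysis without these women as a labelled sensitivity analysis. The clinician's freedom to open the result is a safety provision and is not affected.

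The cost is about one sentence in the protocol and the analysis plan, and one extra analysis. The price is that some FFP decisions taken with knowledge of the result stay in the primary comparison. The sensitivity analysis shows how much they matter.

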#### Subsequent haemostatic therapy

If bleeding continues after the initial 4 units of FFP, the following protocol for blood product usage is suggested but clinicians may deviate from this protocol on a case-by-case basis for any reason:

Red blood cells will be transfused to maintain haemoglobin level above 8 g/dl. Near-patient testing of haemoglobin can be used.

The coagulation screen and FBC should be measured through the routine laboratory and repeated after transfusion of every 4 units of red blood cells or whenever clinically indicated. Point-of-care coagulation testing can be performed and the results acted on according to local practice.

FFP can be transfused in a 1:1 red cell:FFP ratio until bleeding has stopped, irrespective of coagulation results, and even if results are unknown.

In addition, if the PT or aPTT is greater than 1.5 times normal, a further 4 units of FFP can be given if bleeding is on-going. After the first 4 units of FFP, and if the fibrinogen level is less than 1.5 g/l, the cryoprecipitate (10 units) or fibrinogen concentrate at a dose of 60 mg/kg should be administered if bleeding is on-going. If the platelet count is less than 75 × 10^9^/l, 1 adult pool of platelets should be given.

#### Volume replacement

Crystalloid and colloid will be infused at the discretion of the treating clinicians. The colloid will be a gelatine-based product. The volume and time of infusions will be recorded retrospectively from the patient’s notes. The use of colloid hydroxyethyl starches will not be allowed because these interfere with the FIBTEM assay.

#### Postnatal thromboprophylaxis

All women will receive postnatal thromboprophylaxis with low molecular weight heparin. Low molecular weight heparin will be commenced as soon as is practical after bleeding has stopped.

### Setting, location and follow-up

The study will recruit from four centres in the UK. The criteria for selection are based on size of the centres (a minimum of approximately 5500 deliveries per year) and an interest in peripartum clinical studies. The study team at each centre will be based on delivery suite and consist of a lead obstetrician, obstetric anaesthetist and midwife. All obstetricians, obstetric anaesthetists and midwifes at each centre will be involved in the study.

Women recruited to the observational phase, but who do not enter the interventional phase of the study, will be followed up until hospital discharge. Women participating in the interventional phase will be followed up until 6 weeks following randomisation or death. At 6 weeks post-delivery, women who entered the interventional phase of the study will be contacted by telephone. The telephone interview will obtain data on maternal hospital readmissions, incidence of venous or arterial thrombotic events, and initiation and duration of breastfeeding.

### Outcomes and safety measures

The primary outcome is the total number of allogeneic blood products transfused after the study medication until discharge. The total number of allogeneic blood products transfused will be compared between the two arms. Secondary outcomes will be:the proportion of women receiving no allogeneic blood products until discharge and within 24 h after study medication,the number of units of red blood cells, FFP, platelets and cryoprecipitate transfused after study medication within 24 h and until discharge,the volume of cell salvaged blood transfused within 24 h after study medication and until discharge, the total number of units of red blood cells, FFP, platelets and cryoprecipitate transfused within 24 h after the study medication, the total number of units of red blood cells, FFP, platelets and cryoprecipitate plus 1 unit for every 250 ml cell salvage transfused within 24 h after study medication and until discharge, the measured abnormal blood loss within 24 h after study medication and until discharge, the proportion of women requiring cryoprecipitate or fibrinogen concentrate as subsequent therapy within 24 h after study medication and until discharge, the change in Clauss fibrinogen and Fibtem parameters before and 15 min and 24 h after the study medication, the proportion of women requiring invasive procedures (return to theatre, uterine brace sutures, uterine tamponade balloons, radiology intervention and hysterectomy) and the time of this intervention within 24 h after study medication and until discharge, incidence, duration and reasons for not exclusive breastfeeding.

The effects of fibrinogen concentrate infusion on the following safety endpoints will be explored: the proportion of women requiring high dependency and intensive care admission and length of stay, the total length of hospital stay and the incidence of clinically diagnosed arterial and venous thromboembolism within 6 weeks of study medication.

### Statistical methods and data analysis

#### Participant flow and recruitment

Summary statistics on eligibility, recruitment, withdrawal and dropout will be collated for both arms and will form the basis of the CONSORT flow diagram for clinical trial reporting [23], specifically, for each arm, participants randomly assigned, receiving intended intervention, completing the study protocol and analysed for the primary outcome. Any protocol deviations will be described with reasons as well as dates defining the period of recruitment and follow-up.

### Baseline data

Appropriate descriptive summaries and graphical illustrations of demographic and baseline clinical data (pre-study medication) will be presented. Descriptive summaries for selected variables will also be produced at site level. Analyses by study arm will be performed when the data collection for the final randomised patient has been completed and all follow-up data obtained. Baseline data will be used to check comparability between study arms and generalisability of the study population. There will be no formal testing of between-arm differences for any variables at baseline.

### Observational phase

Patients entering the observational phase but not randomised to receive fibrinogen/placebo because of a Fibtem A5 reading ≥16 will be described with regard to demographics and risk factors for PPH (such as pregnancy-related complications, labour and birth details, invasive procedures required to control PPH, bleed volume, transfusion requirement) and compared to the patients in the interventional phase. The whole cohort will be analysed to investigate risk factors for severe PPH and the need for blood transfusion.

